**Introduction**

Since the ancient Thailand, postpartum women sought for lactation stimulating foods and herbs from Thai and Chinese medicine to match their babies’ needs. There were studies outside of Thailand on domperidone that proved its the galactagogue effect. Domperidone was the only galactagogue that had efficacy and safety evidence supported by randomized controlled trials.^1^ However, U.S. Food and Drug Administration (USFDA) recently warned for intravenous form of domperidone.^2,3^ There was no evidence on adverse events for oral form of domperidone.^4^ Thai traditional herbal medicine had potential to be an alternative galactagogue. In Thai traditional medicine, there were several purposes for postpartum herbal uses including promote lochia discharge, blood clot discharge, fundal progression, physical health and lactation. Most herbs for postpartum had acrid properties which promote fire element in the body according to Thai traditional medicine wisdom which stated that human body was comprised of four fundamental elements: earth, water, fire, and wind. A healthy state could be maintained by balance of four fundamental elements while illness or disease was caused by elemental imbalance. Postpartum women lost stamina, water, and blood from delivery which caused imbalance of water, fire and wind elements. Acrid herbs alleviated fire element which promote recovery organ systems in human body.^5^

There were world-wide practices of using herbs for promoting lactation.^6^ Although there was lack of evidence on mechanism of actions, herbal medicine was widely used, varied by traditional wisdom and cultures, had evidence on efficacy and no evidence on major adverse events. There was scarce of study on Thai traditional herbal medicine on promoting lactation. There was only a grey literature on lactation promoting tea consisted of sappan (Caesalpinia sappan Linn.), licorice (Glycyrrhiza glabra Linn.), bale fruit (Aegle marmelos L. Corr), ginger (Zingiber officinale Roscoe), and jewel vine (Glycyrrhiza glabra Linn.), which had lactation promoting, physical promoting, and muscle pain reducing properties, for postpartum women to reduce neonatal jaundice from inadequate breastfeeding. There was reduction on incidence of neonatal jaundice from 10% to 3% and all postpartum women had breast milk production in 24 hours postpartum.^7^

The Wang Nam Yen herbal tea was a promising traditional Thai galactagogue, which might be used as an alternative to the common pharmaceutical galactagogue, domperidone, to support breastfeeding difficulties due to low supply. Domperidone was used as active control with dosage 30 mg/day which evidence proved no difference in human milk production with higher dosage^8^. Women that have undergone cesarean deliveries was selected as population in this study due to cesarean delivery was a risk factor of inadequate breast milk production.^9^

**Methods**

**Study design**

This study is a randomized double blind controlled trial.

**Study population**

Women aged 15 to 41 years who deliver via cesarean section at 28 to 42 weeks’ gestational age.

**Study sample**

Women aged 15 to 41 years who deliver via cesarean section at 28 to 42 weeks’ gestational age at Sunpasithiprasong Hospital, Ubon Ratchathani, Thailand during February 2017 to September 2017.

**Inclusion criteria**

Women aged 15 to 41 years who deliver via cesarean section at 28 to 42 weeks’ gestational age at Sunpasithiprasong Hospital, Ubon Ratchathani, Thailand during February 2017 to September 2017 and provide written informed consent.

**Exclusion criteria**

1. Women who have contraindications for breastfeeding such as human immunodeficiency virus infection
2. Women who have serious peripartum complications leading to inability for breastfeeding such as severe postpartum hemorrhage with hypovolemic shock, cardiac arrest, severe preeclampsia and eclampsia
3. Women with history of domperidone or tea herbal ingredients allergy
4. Women whose neonates are sick and separated from mother

**Sample size calculation**

We use mean and standard deviation of breast milk volume at day 4 after delivery based on the study by based on the study by Jantarasaengaram and Sreewapaon^10^ the effects of domperidone compared to placebo in augmenting lactation following cesarean delivery with 80% power and a 2-sided type I error at 5%

Mean daily milk volume in the domperidone group day 4= 191.3(SD=136.1)

Mean daily milk volume in the placebo group day4 = 91.4 (SD=60.3)

n/group = $\frac{3{(Z\alpha+Z\beta)}^{2}\delta^{2}}{\left( \mu_{1}-\mu_{2} \right)^{2}}$

$\delta=SD of primary outcome$

$$\mu_{1}=191.3 (case group)$$

$$\mu_{2} =91.4 (control group)$$

Consider α = 0.05, Zα = 1.65 Power = 80% Zβ = 0.84

n/group = $\frac{3\left( 1.65+0.84 \right)^{2}{(136.1)}^{2}}{{(191.3-91.4)}^{2}}$

Resulted in n/group = 34.52

With considering an expected follow-up loss of 15%, the anticipated sample size of 120 which would require a sample size of 40 in each group.

1. T– The Wang Nam Yen herbal tea treatment group

2. D– The domperidone treatment group

3. C– The placebo control group

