**Statistical analysis**

The statistical analysis will be performed on an intention-to-treat basis using Stata/MP software version 15.0 (StataCorp 2017, College Station, TX). Descriptive statistics will be carried out using mean with standard deviation for normal distributed continuous data, and median with interquartile range for non-normal distributed continuous data. Categorical data will be presented as counts and percentage and will be tested for significance with Chi-square test. Continuous data will be assessed for normal distribution using histogram and Shapiro–Wilk test. One-way ANOVA with Bonferroni correction will be used for normal distributed continuous data and Kruskall-Wallis test will be used for non-normal distributed continuous data. Significant level is defined as *p*<0.05.

**Figure 3.** Trial procedure

Placing advertisements in four obstetrics wards

Recruiting participant eligible for inclusion and exclusion criteria

Obtaining informed consent from participants

Randomization into 3 groups

| T (n=40)  Wang Nam Yen herbal tea and placebo tablet | D (n=40)  herbal tea placebo and domperidone tablet | C (n=40)  herbal tea placebo and a placebo tablet |
| --- | --- | --- |

Recording baseline data and first administration of intervention at 12-18 hours postpartum

Recording fluid intake and output, numbers of breastfeeding per day, breast milk volume and
drug adverse events at 24, 48 and 72 hours postpartum

Recording primary and secondary outcomes at 72 hours postpartum

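### The 34.52 per group does not follow from the stated two-sided 5% error and 80% power: the calculation uses a one-sided Z and a factor of 3, and these two errors partly offset

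*Protocol*

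**What the plan says.** The protocol, under Sample size calculation, plans the trial "with 80% power and a 2-sided type I error at 5"%. The inputs come from an earlier placebo-controlled trial of domperidone after cesarean delivery:

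- "Mean daily milk volume in the domperidone group day 4= 191.3(SD=136.1")
- "Mean daily milk volume in the placebo group day4 = 91.4 (SD=60.3")

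The calculation then sets "Consider α = 0.05, Zα = 1.65 Power = 80% Zβ = 0.84". It multiplies by 3, uses 136.1 as the only standard deviation, and reports "Resulted in n/group = 34.52". The step to the final number is described as "considering an expected follow-up loss of 15%, the anticipated sample size of 120", that is, 40 in each of the three arms.

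Under Statistical analysis the protocol adds: "One-way ANOVA with Bonferroni correction will be used for normal distributed continuous data". A Kruskal-Wallis test is named for data that are not normally distributed. The number of comparisons to be corrected is not given.

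**The concern.** Three things do not fit together.

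1. **Sidedness.** The declared test is two-sided at 5%, but the Z value entered is the one-sided one.
2. **Multiplier.** The formula compares two means under equal allocation. The variance of that difference is 2 × SD² / n, so the factor is 2. A third arm does not change it, and the protocol gives no reason for the 3.
3. **Multiplicity.** The calculation sizes one contrast at 5%, whereas the analysis section plans a Bonferroni correction.

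The 80% power figure is the only justification given for enrolling 120 women. If it cannot be derived from the declared error rate and the planned analysis, a reader cannot judge how much weight a non-significant result would carry.

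**Working it through.** **Inputs** (Protocol, Sample size calculation): difference 191.3 − 91.4 = 99.9; SD 136.1 (domperidone) and 60.3 (placebo); Zβ = 0.84; 40 per group; 15% loss, so 40 × 0.85 = 34 evaluable.

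**The protocol's own figure**

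3 × (1.65 + 0.84)² × 136.1² / 99.9² = 3 × 6.2001 × 18523.21 / 9980.01 = 34.52. It reproduces. 34.52 × 1.15 = 39.7, which gives 40.

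**Correcting each error**

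| Z | Factor | n per group |
| --- | --- | --- |
| 1.65 | 3 | 34.5 (as written) |
| 1.65 | 2 | 23.0 |
| 1.96 | 3 | 43.7 |
| 1.96 | 2 | 29.1 |

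The last row matches the declared test: 2 × (1.96 + 0.84)² × 136.1² / 99.9² = 29.1, so 30 evaluable. 30 / 0.85 = 35.3, so 36 per group and 108 in total.

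The written formula equals the correct one with a Z of √1.5 × 2.49 − 0.84 = 2.21. That is a two-sided level of about 0.027, which the protocol states nowhere.

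**Power of the planned size, one contrast, unadjusted two-sided 5%**

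Noncentrality with 34 per group: 99.9 / (136.1 × √(2/34)) = 3.03. The noncentral t distribution with the three-group error degrees of freedom (3 × 34 − 3 = 99) gives 85.0%. The normal approximation gives 85.7%.

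**Power with Bonferroni correction**

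The number of comparisons is an assumption: three for all pairs (0.05/3 = 0.0167) or two for each active arm against placebo (0.05/2 = 0.025).

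| SD | Analysed per group | Comparisons | Power, noncentral t | Power, normal approx. |
| --- | --- | --- | --- | --- |
| 136.1 | 34 | 3 | 72.2% | 73.6% |
| 136.1 | 34 | 2 | 77.2% | 78.4% |
| 136.1 | 40 | 3 | 80.2% | 81.3% |
| 105.3 | 34 | 3 | 93% | 93.6% |

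The 105.3 uses both stated standard deviations: √((136.1² + 60.3²)/2). With SD 136.1 and three comparisons, the number needed is 2 × (2.394 + 0.84)² × 136.1² / 99.9² = 38.8, so 39 evaluable and 39 / 0.85 = 45.9, or 46 per group.

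**The case against.** The strongest reply is that the errors do no harm. They offset towards a larger trial, and at the declared two-sided 5% the planned size gives more than the promised 80%. This is correct and stands. It means that 120 women need not be changed. It does not make the derivation right, because the surplus is accidental and the stated figures still contradict each other.

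A reader might infer that the trial is underpowered because Bonferroni was ignored. The protocol does not establish that. The 72% needs the larger SD in both arms, the full 15% loss and all three pairs corrected. Relaxing only the loss gives about 80%, and using both stated SDs gives about 93%. The analysis sentence is also generic: Kruskal-Wallis would replace the ANOVA for non-normal data, and which contrasts are corrected may be settled in a statistical analysis plan that is not at hand. What remains is that the sample size section makes no allowance for a correction that the same protocol plans.

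A reader might also correct the Z value alone, get 43.7 (44 evaluable, 52 per group) and conclude that the trial is far too small. That keeps the wrong factor of 3 and overstates the case.

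Finally, the dropout step could be criticised: 34.52 / 0.85 = 40.6 rather than 39.7. This is one woman per arm and nothing depends on it.

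**Conclusion.** The written derivation is wrong. It pairs a declared two-sided 5% error with the one-sided Z, and uses a factor of 3 where 2 belongs. With both corrected, the protocol's inputs require 29.1 evaluable per group, not 34.52. The planned 40 per group (34 evaluable) have about 85% power for one contrast of 99.9 with SD 136.1 at unadjusted two-sided 5%.

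Under the planned Bonferroni correction, power lies between about 72% and about 93% across the assumptions shown. Whether it falls below 80% depends on choices that the protocol leaves open, so neither a shortfall nor adequate power can be stated flatly.

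One might take the 85% as the power for the tea against placebo. The protocol does not support that. The inputs are domperidone and placebo daily volumes at day 4, no effect is given for the tea, and the primary outcome under Outcome measures is the volume from one timed pumping session at 72 hours. The figures carry over only on an explicit assumption.

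**What to change.** Keep 120 women and rewrite the sample size section as follows.

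1. Restate the calculation as 2 × (1.96 + 0.84)² × 136.1² / 99.9² = 29.1, so 30 evaluable and 36 per group after dividing by 0.85. State that 40 per group, with 34 evaluable, gives about 85% power for one domperidone-sized contrast at unadjusted two-sided 5%.
2. Add the power under the planned Bonferroni analysis as a range, with each assumption named. With SD 136.1 and 34 evaluable: about 72% for three comparisons and 77% for two. With SD 136.1 and all 40 analysed: about 80% for three. With both stated SDs and 34 evaluable: about 93% for three.
3. State that these figures hold for tea against placebo only if the tea is assumed to have the domperidone effect, and that the inputs are daily volumes at day 4.

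The cost is rewording one section, with no extra participants. The only downside is that the stated power becomes less favourable than 80% under some of the assumptions.

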**Randomization**

Participants will be random allocated into 3 groups with 1 : 1 : 1 ratio by block randomization with block of three using table of random numbers for creating randomization ID which will be enveloped in opaque envelop to mask clinicians, data collectors and patients.

Randomization ID will be assigned as

A = T– The Wang Nam Yen herbal tea treatment group which will receive Wang Nam Yen herbal tea and placebo tablet after each meal for three meals per day.

B = D– The domperidone treatment group which will receive herbal tea placebo and a 10 mg domperidone tablet after each meal for three meals per day.

C = C– The placebo control group which will recieve both herbal tea placebo and a placebo tablet after each meal for three meals per day.

There will be 6 possible blocks of three including 1 = ABC, 2 = ACB, 3 = BAC, 4 = BCA, 5 = CAB และ 6 = CBA

When 120 randomization ID are generated, the ID will be joined together starting with randomization ID for participant number 9 (TD009) as the first ID.

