**Trial procedure**

1. Literature review for relevant studies.
2. Drafting trial protocol and design case record form for ethical committee approval.
3. Plan for education for standard postpartum care and breastfeeding to women aged

15 to 41 years who deliver via cesarean section at 28 to 42 weeks’ gestational age at Sunpasithiprasong Hospital, Ubon Ratchathani, Thailand during February 2017 to

September 2017 and provide written informed consent.

1. Recruiting participants according to inclusion and exclusion criteria by placing advertisements in four obstetrics wards.
2. Giving trial information to potential participants using obstetrician and nurse in each obstetric ward and participant information sheet to confirm participant understanding of trial objective, procedure, benefits, and risks. If potential participants are willing to participate in trial, they will be asked to sign informed consent form with understanding that they can quit from trial at any time without any consequence.
3. Participants will be randomly assigned into three groups based on numbers generated by a table of random numbers in blocks of three: 1) Wang Nam Yen herbal tea and placebo tablet (T group), 2) domperidone tablet and placebo herbal tea (D group), 3) placebo tablet and placebo herbal tea (C group).
4. All study interventions will be prepacked and sealed in opaque packages, for three consecutive days of postpartum use. Participants and investigators were blinded to the treatment assignment. Randomization ID will be TD001 to TD120.

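### The fixed block of three, printed in the protocol with all its orders, makes allocations deducible if masking fails; the unexplained TD009 start needs a minor clarification

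*Protocol*

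**What the plan says.** The Randomization section of the protocol states: "Participants will be random allocated into 3 groups with 1 : 1 : 1 ratio by block randomization with block of three". It then lists the orders: "There will be 6 possible blocks of three including 1 = ABC, 2 = ACB, 3 = BAC", and so on to the sixth. Trial procedure repeats the block size of three.

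On the list itself, the Randomization section continues "When 120 randomization ID are generated", and then "the ID will be joined together starting with randomization ID for participant number 9 (TD009) as the first ID". Trial procedure says "Randomization ID will be TD001 to TD120", and the example envelope and insert in the Blinding section both carry TD001. No reason is given for beginning at the ninth ID, and nothing is said about TD001 to TD008.

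On masking, the protocol provides opaque sealed envelopes, an envelope opener who is neither clinician nor data collector, and prepacked opaque supplies. Both the tea and the tablet have a placebo. The placebo tea bag and the placebo tablet are described as identical to the active ones. The taste, colour and smell of the brewed placebo tea are not described, and its contents are not given.

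**The concern.** With three arms and blocks of three, each block holds each arm exactly once. Anyone who learns two allocations in a block has the third without opening an envelope. Because the size and all six orders are in the protocol, no guesswork about the scheme is needed.

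Two things could suffer. If a coming allocation can be foreseen, the choice of whom to approach, or when, can be influenced; ward obstetricians and nurses are the ones who give trial information to potential participants. If two women in a block have been unmasked, the third is unmasked as well, even after she has been allocated.

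The most likely leak is the drink. The active tea contains ginger, licorice and sappan, and it is taken three times a day on the ward.

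The TD009 instruction raises a smaller question: a reader cannot tell from the text how the list of 120 is ordered or whether its blocks stay whole.

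**Working it through.** **List length.** The Sample size calculation gives 3 × (1.65 + 0.84)² × 136.1² / (191.3 − 91.4)² = 34.52 per group, which reproduces. Adding 15% gives 34.52 × 1.15 = 39.7, so 40 per group and 3 × 40 = 120 in total. That is 120 / 3 = 40 complete blocks. The formula is used here only to confirm the length of the list.

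**Full knowledge of earlier arms.** Once the first two letters of any of the six orders are known, the third is fixed in 6 of 6. That is one allocation per block, or 40 of 120. A guesser who knows all earlier arms in the block is right with probability 1/3, 1/2 and 1 at positions 1, 2 and 3. The average is (1/3 + 1/2 + 1) / 3 = 61.1%, against 33.3% by chance.

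**Knowledge of tea versus placebo tea only.** Arms D and C both receive placebo tea, so recognising the drink separates T from the rest and no more. Six orders of three positions give 18 positions. Whether the next woman gets tea is certain as follows:

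- Position 1: never, 0 of 6.
- Position 2: only if position 1 was tea, 2 of 6.
- Position 3: always, 6 of 6.

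Total: 8 of 18 = 44%.

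**The same count for larger blocks.** A position is certain when the remaining places in the block are all tea or all non-tea. With k tea places and 2k others, the expected number of such positions per block is 2k/(k + 1) + k/(2k + 1).

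| Block size | k | Certain positions per block | Share |
|---|---|---|---|
| 3 | 1 | 1 + 1/3 = 1.33 | 44% |
| 6 | 2 | 4/3 + 2/5 = 1.73 | 29% |
| 9 | 3 | 6/4 + 3/7 = 1.93 | 21% |

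These shares assume that the guesser knows the block size and where each block starts. Random, undisclosed sizes remove that knowledge.

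**The TD009 start.** If blocks are cut from TD001, block 3 is TD007 to TD009, so TD009 is its last position. The text admits three readings:

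- The list is rotated (TD009 to TD120, then TD001 to TD008). All 120 IDs and 40/40/40 are kept; one block is split across the two ends.
- TD009 is the label of the first code generated. No block is broken, but labels would run to TD128 (9 + 119), which does not fit TD120.
- TD001 to TD008 are discarded. Then 120 − 8 = 112 = 37 × 3 + 1, giving arms of 38/37/37.

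**The case against.** The strongest reply is that concealment is already addressed. Codes are sealed and opaque, the opener has no clinical or data role, supplies are prepacked, and both treatments have placebos. A fixed block in such a trial is not an error, and a block size written in a protocol does not show that recruiters read it. All of this stands, and it is why the weakness is conditional. Two gaps remain: the brewed drink is not stated to be matched, and the protocol does not say that the opener, who sees each assignment, is kept apart from recruitment.

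It is also fair to say that recognising the tea does not give the third woman's exact arm unless T comes last, in 2 of the 6 orders. The 44% therefore refers only to tea versus no tea. Recruitment runs across four wards, so staff on one ward may see only part of a block.

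A reader might infer from the TD009 sentence that eight IDs are lost, only 112 allocations remain and power suffers. The text does not support this. It speaks of joining 120 generated IDs with TD009 first, which fits a rotated list with 40 per arm, and nowhere says that any ID is discarded. Even on the discard reading, 37 or 38 per arm less 15% leaves about 31 or 32. With the protocol's difference of 99.9 and SD of 136.1, noncentral-t power for one two-sided 5% comparison is then 0.811 or 0.824, still above the 80% target. A reader might also infer that the sections disagree on which arm an ID carries. On the rotated reading, each envelope keeps its own code and only the order of use changes.

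**Conclusion.** The block-size point holds as a conditional weakness that is cheap to reduce. If two arms in a block become known, the third is certain, without exception. If only the tea is recognised, 44% of block positions are certain for tea versus no tea. That figure is an upper value. It assumes that the guesser recognises the drink without error, knows the block boundaries, and knows the tea status of every earlier woman in the block before the next is allocated. The protocol gives no evidence that this happens, and nothing here shows bias.

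The TD009 start is a minor clarification: the Randomization and Trial procedure sections need reconciling. No loss of sample size or power should be claimed from it.

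**What to change.** Before enrolment, generate the list of 120 with randomly varied block sizes, for example 3, 6 and 9, ending on a complete block. Remove the block size and the printed orders from the Randomization section, remove the block size from Trial procedure, and keep them in a document that ward staff do not see.

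Replace the TD009 instruction with a statement that all 120 IDs, TD001 to TD120, are used in complete blocks. If there is a reason for starting at TD009, give it and say where TD001 to TD008 fall.

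The cost is a regenerated list and edits to two short paragraphs. If recruitment stops mid-block, arms can differ by at most three (a block of nine holds three of each arm), against at most one with blocks of three.

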**Blinding**

After generating randomization codes, the research team which responsible for blinding will create opaque envelope to seal the randomization codes. The front end of an opaque sealed envelope will present study name, principal investigator name, site of study, randomization ID, study ID, and date which envelope will be opened (Figure 1).

Study : Efficacy of Wang Nam Yen Herbal Tea on Breast Milk Production : A Factorial Randomized Controlled Trial (Tea4Milk)

PI : [name]

Site : Sunpasitthiprasong hospital

Randomization ID : TD001

Study ID : ________________________________________

Date envelope opened : ____________________________

**Figure 1.** Example of the front end of an opaque sealed envelope

There will be a document inside the sealed envelope with randomization ID, assigned group, study ID, date and time which envelope will be opened, and signature of envelope opener who are not clinician nor data collector (Figure 2).

Randomization ID : TD001

Assessment group :

Study ID : ________________________________________

Date envelope opened : ____________________________

Time envelope opened : ____________________________

Signature the person who randomizing the subject :

________________________________________________

**Figure 2.** Example of the document inside an opaque sealed envelope

